### **Description of the treatments**

All study drugs will be given according to standard operation procedures (SOP) established at the CRSN. The group AS-AQ-MB will receive once daily one tablet of the fixed dose AS-AQ (Coarsucam®, Sanofi Aventis, taken from the quality-controlled stock of the Ministry of Health) using three weight groups (6.0 – 8.9 kg: 25 mg AS + 67.5mg AQ; 9.0-17.9 kg: 50 mg AS + 135 mg AQ;  $>17.9$  kg: 100 mg AS + 270 mg AQ), combined with once daily MB (15 mg/kg) mini-tablets using four weight groups (6.0-8.9 kg: 100 mg MB; 9.0-12.9 kg: 150 mg MB; 13.0-16.9 kg: 200 mg MB;  $>16.9$  kg: 250 mg MB) given over a three days period. Each mini-tablet contains 2 mg MB. Coarsucam® tablets will be taken with water. For patients unable to swallow the tablets whole, e.g. very young children, the tablets can be dissolved in water before administration. The tablets can also be crushed and administered with water. The MB treatment will be provided on a spoon with local food to increase the acceptability for the

## **Artesunate – Amodiaquine - Methylene blue – Phase II Clinical Trial Protocol**

children. The PQ tablets will be dissolved in drinking water and given with a plastic cup or spoon, also together or after some food.

Justification: Coarsucam® in the given dosing schedule is the standard of care for the treatment of uncomplicated malaria in Burkina Faso. MB has been used for treatment of young children in Burkina Faso in a number of studies in recent years with dosing regimens ranging from 4 - 24 mg per kg per day over a three days period (twice daily applications with doses ranging from 2 - 12 mg per kg), without any obvious safety problem. Daily MB dosing between 12 and 24 mg per kg was demonstrated to be safe and effective in a dose finding study. The half-life being 20 hours, MB in the dosage of 15 mg per kg per day given as single dose has recently been shown to be safe and effective.

The MB minitablets are a newly developed solid formulation developed at the Heinrich Heine University Düsseldorf in Germany and produced by the company Pharbil Waltrop GmbH in Waltrop, Germany, under GMP conditions. The formulation is based on the recently introduced principle of orodispersible minitablets that dissolve rapidly - within less than 10 seconds - in the oral cavity which prevents aspiration / inhalation of particles (Stoltenberg 2011). The produced mini-tablets are directly compressed, round, biconvex, blue minitablets of 2 mm in diameter and height and contain 2.0 mg Methylene Blue as the active pharmaceutical ingredient. Further ingredients are the following excipients of pharmaceutical grade: Ludiflash™ (containing mannitol, crospovidone and polyvinyl acetate) and magnesium stearate. For Ludiflash™, the manufacturer and supplier has released a paediatric dossier showing the applicability of the ingredients in the paediatric population at all age groups (Hebestreit 2010). Magnesium stearate is generally regarded as safe (GRAS status), as well for paediatric use. Recent data from the University of Düsseldorf show that the use of mini-tablets in children below 6 years is not only safe, but even better accepted than the use of sweet, well-tasting liquids (Klingmann 2015). The new concepts with multiparticulates manufactured on simple, standard pharmaceutical equipment (mixer and rotary tablet machine) fits perfectly with the recently published recommendations of WHO initiative “Making medicines child-size”. For the present study, the Methylene Blue mini-tablets should be dispersed in a semi-solid food stuff such as pudding or yoghurt. When suspended in the semi-solid food, the mini-tablets mainly keep the geometry without disintegration, but they remarkably soften and are neither recognised as solid drug carriers in the mouth nor show any risk of aspiration.

The control group will receive once daily one tablet of the fixed dose AS-AQ (Coarsucam®, Sanofi Aventis) using three weight groups (6.0 – 8.9 kg: 25 mg AS + 67.5mg

## **Artesunate – Amodiaquine - Methylene blue – Phase II Clinical Trial Protocol**

AQ; 9.0-17.9 kg: 50 mg AS + 135 mg AQ; >17.9 kg: 100 mg AS + 270 mg AQ), given over a three days period. In addition, on day 2 the children of this group will receive a single dose of 0.25 mg/kg PQ (Sanofi, India) using four weight groups (6.0 – 8.9 kg: 2 mg PQ; 9.0-12.9 kg: 3 mg PQ; 13.0-16.9 kg: 4 mg PQ; >17.0 kg: 5 mg PQ).

All children having fever (temperature  $\geq 38.5^{\circ}\text{C}$ ) will receive standard doses of paracetamol (= acetaminophen; 10 mg/kg every 6 hours) until symptoms subside.

Study children developing severe malaria during the trial will be admitted to the Nouna hospital and treated with quinine according to national guidelines. Study children developing uncomplicated malaria recrudescence or reinfection or who show asymptomatic parasitological failure during follow-up between day 7 and day 28 will be treated with artemether-lumefantrine according to national guidelines.

### **Drug storage and drug accountability**

The investigator, or his designated deputy (e.g. nurse or pharmacist), will make sure that the Investigational Products are adequately stored in a secured area with restricted access, under recommended storage conditions by the manufacturer and in accordance with applicable regulatory requirements. Prior to dispensing, all study medications should be stored by the investigator between 20 °C and 30 °C. The investigator must record the receipt and usage of all drugs supplied.

A drug accountability utilisation log will be maintained for clinical trial material by the investigator. This will include the date and time of administration, the quantity administered and the patient randomisation number. The log should be signed and dated by the investigator.

### **Permitted and not permitted concomitant treatments**

All indicated drugs are allowed, except other western malaria drugs including antibiotics with malaria efficacy (e.g. cotrimoxazole, doxycycline, acythromycine) and except serotonin reuptake inhibitors (e.g. citalopram, escitalopram, fluoxetine, paroxetine, sertraline) and drugs known to inhibit the liver enzymes cytochrome 2A6 (e.g. methoxsalen, pilocarpine, tranylcypromine) and/or cytochrome 2C8 (e.g. trimethoprim, ketoconazole, ritonavir, saquinavir, lopinavir, gemfibrozil, montelukast) from beginning of treatment until end of follow-up.

### **Prior and concomitant illnesses**

## **Artesunate – Amodiaquine - Methylene blue – Phase II Clinical Trial Protocol**

Prior illnesses based on self-reporting of parents/caretakers will be recorded as relevant to the current condition, mainly for the last 7 days. All concomitant illnesses will be recorded based on the examination of the study physicians during the 28 days observation period. Concomitant illnesses between visits will be recorded based on reports from interim hospital visits of study children and/or based on self-reporting of parents/caretakers.

### **Procedures for monitoring subject compliance**

Drug intake will be directly observed and assisted by the study nurses or specific field staff for the whole treatment period. In case of vomiting within 1/2 hour after first drug ingestion, the treatment dose will be repeated. In case of further vomiting, the child will be withdrawn from the study and treated according to local standards.

### **Visits and follow-up**

All parents/caretakers are informed that they should return to the study centres for further examination and treatment in case that the child again develops a significant illness between the first treatment dose and the final visit on day 28. The addresses of all study subjects will be recorded at enrolment of study children, and all children having not returned for one of the scheduled follow-up visits will be visited at home.

### **Methods of data collection**

Haemoglobin (day 0, day 1, day 2, day 3, day 7, day 14, day 28, day X), parasitaemia (day 0, day 1, day 2, day 3, day 7, day 14, day 28, day X), and filter paper samples for determination of G6PD status (day 0), PCR genotyping of malaria parasites (day 0, day 7, day 14, day 28, day X) will systematically be collected (day X is any unscheduled visit between day 3 and day 28). Whenever possible, finger prick blood samples will be taken instead of venous blood samples. Temperature will systematically be measured during all time points with electronic thermometers. On day 7, 14, and 28, self-reported signs and symptoms and any traditional and western treatment taken will systematically be recorded.

## **Study Plan**

## **Artesunate – Amodiaquine - Methylene blue – Phase II Clinical Trial Protocol**

|                              | Inclusion/
Treatment |    |    | Follow up |    |     |     | Unscheduled
visit |
|------------------------------|-------------------------|----|----|-----------|----|-----|-----|----------------------|
|                              | D0                      | D1 | D2 | D3        | D7 | D14 | D28 | Day X                |
| Informed consent             | •                       |    |    |           |    |     |     |                      |
| Physical Examination         | •                       | •  | •  | •         | •  | •   | •   | •                    |
| Inclusion/exclusion criteria | •                       |    |    |           |    |     |     |                      |
| Blood smears                 | •                       | •  | •  | •         | •  | •   | •   | •                    |
| PCR samples for              |                         |    |    |           |    |     |     |                      |
| G6PD status                  | •                       |    |    |           |    |     |     |                      |
| recrudescence/reinfection    | •                       |    |    |           | •  | •   | •   | •                    |
| Study drugs                  | •                       | •  | •  |           |    |     |     |                      |
| Concomitant medication       | •                       | •  | •  | •         | •  | •   | •   | •                    |
| Adverse events               | •                       | •  | •  | •         | •  | •   | •   | •                    |
| Haematology                  | •                       | •  | •  | •         | •  | •   | •   | •                    |
| Fever                        | •                       | •  | •  | •         | •  | •   | •   | •                    |

### **7 Assessment of primary endpoint**

- Haemoglobin values will be determined by measurement with HemoCue® at baseline and on day 7.

### **8 Assessment of secondary endpoints**

- Gametocyte prevalence and density will be measured microscopically at baseline and on day 1, 2, 3, 7, 14, and 28 of follow-up
- Parasite clearance time (time between inclusion and clearance of parasites), measured through microscopic determination on day 1, day 2, and day 3.
- Fever clearance time (time between inclusion and clearance of fever), measured with electronic thermometers on day 1, day 2, and day 3.
- ACPR, ETF, LPF and LCF will be determined over the 28 days study period according to the standard WHO protocol (WHO 2003)
- Reports of observed or self-reported adverse event (definition below)
- Reports of patients with at least one serious adverse event:
  1. Acute haemolysis (definition: haemoglobin  $\leq$  5 g/dl, or received blood transfusion according to clinical judgement of study physician)
  2. Other serious adverse events (definition below)
- Change in haemoglobin after 2, 3, 14, 28 days compared to baseline
- Acceptance of the different treatment regimens by mothers/caretakers

**Methods of data collection**

Data on the occurrence of adverse events (severity, seriousness and causality), malaria recrudescence/reinfection, concomitant illnesses and concomitant drugs will be collected through continuous active and passive clinical surveillance (including laboratory results) of all study subjects.

*The following laboratory methods will be employed:*

Haemoglobin concentrations will be measured in the field using a HemoCue® (HemoCue® AB, Angelholm, Sweden), and malaria parasites will be diagnosed with standard techniques by light microscopy (laboratory of CRSN).

Differentiation of recrudescences from new infections will be achieved by comparing PCR-generated *msp1* and *msp2* genotype patterns in matched pairs of isolates obtained on admission and precisely on the day of reappearance of parasitaemia, also based on filter paper blood samples (Snounou et al. 1999) (Laboratory of Tropical Institute Berlin).

The common West African G6PD deficiency allele GdA- will be distinguished from GdA and GdB by PCR methodology, also based on filter paper blood (Laboratory of Tropical Institute Berlin).

An overall statistical analysis plan will be prepared before the database is closed.

**Adverse event (AE) definition**

The term “adverse event” covers any sign, symptom, syndrome and illness that appears or worsens in a subject during the period of observation in the clinical trial and that may impair the well-being of the subject. The term also covers laboratory findings or results of other diagnostic procedures that are considered to be clinically relevant.

No causal relationship with the study medication is implied by the use of the term “adverse event”. Adverse events fall into the categories Of non-serious and serious.

**Serious adverse event (SAE) definition (GCP)**

A serious adverse event is defined as any untoward medical occurrence at any dose: (1) results in death, (2) is life-threatening, 3) requires inpatient hospitalisation or prolongation of existing hospitalisation, (4) results in persistent or significant disability/incapacity (5) is a congenital anomaly / birth defect. (“Life-threatening” refers to an event in which the patient

## **Artesunate – Amodiaquine - Methylene blue – Phase II Clinical Trial Protocol**

was at risk of death at the time of the event; it does not refer to an event which hypothetically might have caused death if it was more severe).

### **Classification of severity**

Mild: The adverse event does not interfere with the routine activities. The patient may experience slight discomfort.

Moderate: The adverse event interferes with routine activities. The patient may experience significant discomfort.

Severe: The adverse event makes it impossible to perform routine activities. The patient may experience intolerable discomfort or pain.

### **Classification of causality**

Unrelated, possibly related, probably related, definitely related; cannot be assessed, for instance due to lack of information.

### **Unexpected adverse reaction (UAR) (EU Directive 2001/20/EC of 4 April 2001)**

An adverse reaction, the nature or severity of which is not consistent with the applicable product information.

### **Period of observation of adverse events**

This is the period between the informed consent and the final examination on day 28.

### **Documentation of adverse events and serious adverse events**

All adverse and serious adverse events will be recorded on specific forms. The adverse event form contains a detailed description of the adverse event (type of event, beginning and duration, severity, outcome, causality to the study medication, specific therapy), serious adverse event (yes/no), and date and signature of the attending physician. For serious adverse events (SAEs) a description of the SAE and consequences for the trial are documented.

### **Reporting of serious adverse events**

Serious adverse events have to be reported by the attending physician to the principle investigators within 24 hours or not later than the next working day. The SAE is also reported to both of the independent Ethic Committees (Heidelberg and Burkina Faso) as per their requirements.

### Early termination of the trial

Reasons that may require the termination of the trial include the following: (1) Incidence of adverse events indicates a potential health hazard caused by the study treatment. (2) It appears that participant's enrolment or study logistics are unsatisfactory. (3) External evidence that makes it necessary to terminate the trial. The steering committee will decide on an early termination.

## **9 Statistics**

### Analysis sets

The primary efficacy analysis will be based on the full analysis set (FAS) according to the intention-to-treat (ITT) principle, reflecting the recommendations given in guidelines (e.g. ICH Harmonised Tripartite Guideline, 1999). Furthermore, in 2005 Brittain and Lin demonstrated that the ITT and the per-protocol (PP) set yield almost identical results. Thus, ITT should be preferred as the primary efficacy set here. Additionally, an evaluation of the primary outcome will be performed in the PP set, in accordance to Snapinn in 2000, where the importance of the PP set in non-inferiority trials was emphasised. Before database closure the assignment of each patient to the PP and the ITT population are defined in the statistical analysis plan.

The safety set will consist of all patients who received one of the study treatments at least once, and patients will be allocated to the treatment they actually received. This will be the primary analysis set for the safety analysis.

### *Confirmatory analysis*

The hypotheses for the primary efficacy analysis are

$$H_0: \mu_{PQ} - \mu_{MB} \geq \delta \text{ vs. } H_1: \mu_{PQ} - \mu_{MB} < \delta$$

( $\delta=0.7$ , non-inferiority margin), where  $\mu_{MB}$  and  $\mu_{PQ}$  are the mean differences in haemoglobin between day 7 and baseline for the AS-AQ-MB and the AS-AQ-PQ group, respectively. Non-inferiority of AS-AQ-MB as compared to AS-AQ-PQ will be tested at one-sided significance level of  $\alpha=0.025$ . Missing data for the primary outcome variable will be replaced using multiple imputation (van Buuren, 2012) taking the covariates treatment group and baseline haemoglobin into account by application of the fully conditional specification method (van Buuren, 2007). This will be realised using the option “FCS” of the SAS “MI” procedure which is

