### **Sample size**

The sample size calculation is based on the primary comparison of the mean change in haemoglobin (day 7 – baseline) between the two treatment groups. 50 patients per arm are needed to assess non-inferiority of AS-AQ-MB to AS-AQ-PQ with a power of 80% at a one-sided significance level of 2.5%, with allowance for 10% loss to follow-up and with the use of a clinically relevant non-inferiority margin of  $\delta=0.7$ , assuming a standard deviation of 1.1722 in both groups (estimate based on own unpublished data from Coulibaly et al. 2015). Thus, the overall number of study patients is 100. Sample size calculation was performed using ADDPLAN v6.1.

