## **Artesunate – Amodiaquine - Methylene blue – Phase II Clinical Trial Protocol**

implemented in SAS 9.4. Sensitivity analyses will be performed by applying alternative methods dealing with missing data such as, e.g. complete case analysis and replacement by ICA-r (Higgins, 2008). Additionally, a linear regression model will be fitted for a comparison of the mean haemoglobin differences rates between the treatment groups adjusting for baseline haemoglobin.

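### The confirmatory imputation of day-7 haemoglobin change leaves out the day 1–3 haemoglobin values already collected, so loss that follows early falls unequally in the two arms would bias the comparison.

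*Protocol*

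**What the plan says.** Protocol section 9, Confirmatory analysis, defines the primary outcome as the change in haemoglobin from baseline to day 7. It then states: "Missing data for the primary outcome variable will be replaced using multiple imputation". The predictors are named in the same sentence: "taking the covariates treatment group and baseline haemoglobin into account by application of the fully conditional specification method".

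Section 6, Methods of data collection, lists the measurement days as "Haemoglobin (day 0, day 1, day 2, day 3, day 7, day 14, day 28, day X", the last being any unscheduled visit. The Study Plan table agrees. The post-baseline values other than day 7 appear only among the secondary outcomes, in section 8: "Change in haemoglobin after 2, 3, 14, 28 days compared to baseline".

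The sensitivity analyses named for missing data are "alternative methods dealing with missing data such as, e.g. complete case analysis and replacement by ICA-r". Neither is described as using the other haemoglobin days. The additional regression adjusts for baseline haemoglobin alone.

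**The concern.** The primary question is whether MB lowers haemoglobin relative to PQ. The protocol watches for early falls: it measures haemoglobin daily to day 3, and its Definitions table defines haemolysis by a drop within 24 hours. If a child has fallen by day 3 and then misses day 7, that fall is likely to say something about the missing value. The named imputation model does not use it.

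Multiple imputation under missing at random is only as good as the variables it conditions on. Given arm and baseline alone, the assumption fails whenever loss depends on the early course. Whether that failure reaches the treatment difference depends on whether it is the same in both arms. If it differs, the confirmatory test no longer has its stated error rate, and the trial has already paid for the data that would repair it.

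**Working it through.** **Inputs from the protocol.** Margin 0.7 (unit not given; taken as g/dl, the unit used for haemoglobin elsewhere), "assuming a standard deviation of 1.1722 in both groups", 50 children per arm, 10% loss to follow-up, and the design "with a power of 80% at a one-sided significance level of 2.5" per cent.

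**The plan's own figure.** Normal approximation: n = 2 × (1.960 + 0.842)² × 1.1722² / 0.7² = 44.02, so 45 per arm. Exact non-central t power at 45 is 80.0%. Allowing for loss, 45 / 0.9 = 50. The sample size reproduces and is not in question.

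**Assumptions not in the protocol.** The correlation ρ between the day-3 and day-7 changes is taken as 0.5 to 0.8. The missingness mechanisms are those described below.

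**One child.** Take a child 2 SD below the mean change on day 3. Its expected day-7 change lies 2 × ρ × 1.1722 below the mean: 1.17 g/dl at ρ = 0.5 and 1.88 g/dl at ρ = 0.8. The two-covariate model places no part of that shortfall in the centre of the imputation distribution.

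**Expected shift in the arm difference.** If only the MB arm loses children selectively, the shift is approximately ρ × 1.1722 × E[z | observed], where z is the standardised day-3 change. With missingness logistic in z:

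- Odds ratio 2 per SD lower (intercept −2.4, about 10% lost): E[z | observed] = 0.065. Shift 0.5 × 1.1722 × 0.065 = 0.04 and 0.8 × 1.1722 × 0.065 = 0.06.
- Odds ratio 5 per SD lower (intercept −3.2, about 9% lost): E[z | observed] = 0.115. Shift 0.07 and 0.11.

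The MB mean is overstated, so PQ minus MB falls, which is towards non-inferiority.

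**Simulation.** 50 per arm, about 10% missing, 20 imputations combined by Rubin's rules, 2,500–3,000 replicates, true difference at the margin. Each cell gives the bias in PQ minus MB and the one-sided error.

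| Loss mechanism | ρ | Arm + baseline | Day 3 added |
|---|---|---|---|
| Random | 0.5 | 0.00; 2.8% | 0.00; 2.7% |
| Random | 0.8 | 0.01; 2.1% | 0.01; 1.9% |
| Day-3 dependent, both arms, OR 2 | 0.5 | 0.01; 2.3% | 0.01; 2.2% |
| Day-3 dependent, both arms, OR 2 | 0.8 | −0.01; 2.4% | −0.01; 2.7% |
| MB only, OR 2 | 0.5 | −0.03; 3.4% | 0.00; 2.5% |
| MB only, OR 2 | 0.8 | −0.06; 3.9% | 0.00; 2.4% |
| MB only, OR 5 | 0.5 | −0.07; 4.4% | 0.00; 2.5% |
| MB only, OR 5 | 0.8 | −0.11; 5.7% | 0.00; 2.2% |

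Simulation error is about 0.245/√3000 = 0.004 g/dl for the bias and √(0.025 × 0.975/3000) = 0.3 percentage points for a 2.5% error rate.

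A second set of runs used a haemoglobin SD of 1.5 and correlations of 0.69 (day 0 with 7), 0.80 (0 with 3) and 0.85 (3 with 7). MB-only loss gave −0.04 to −0.05 (OR 2) and −0.09 to −0.10 (OR 5), with errors of about 3.6% and 6.2%. Selective loss in the PQ arm only, at OR 5, gave about +0.09, against non-inferiority. Equal selective loss in both arms gave 0.00.

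**Extreme bound.** Suppose the lowest 10% on day 3 are all lost from MB and none from PQ. The shift is ρ × 1.1722 × φ(z₀.₁)/0.9 = ρ × 1.1722 × 0.195, that is 0.11 to 0.18 g/dl. The standard error is 1.1722 × √(1/50 + 1/45) = 0.241, so the one-sided error is about 7% to 11%.

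**Precision under random loss.** Adding day 3 lowers the empirical standard error from 0.251 to 0.247 at ρ = 0.5 and from 0.241 to 0.233 at ρ = 0.8.

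**Complete-case analysis.** In the second set of runs it was biased in the same direction as the two-covariate imputation and slightly more (about −0.05 and −0.10 at 10% loss), so it would not expose the problem.

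**The case against.** A reader might infer that the model is biased towards declaring MB non-inferior. The documents do not support that. Bias needs loss that relates to early falls differently by arm, and nothing in the protocol says MB children who fall will be the ones to leave. Section 3 attaches the feared haemoglobin drop to PQ, at high or prolonged dosing in G6PD deficiency, and reports no clinically relevant drop across more than 1,000 children in MB trials. Selective loss in the PQ arm would push the result the other way. This objection stands. Against it, the trial is open label to families, MB colours the urine and tastes bitter, and the two drugs are given on different days, so unequal loss is possible, though not shown.

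Retention measures also weaken the mechanism: home visits after a missed appointment, permanent residence as an entry condition, and free care. The one withdrawal the protocol requires, repeated vomiting at the first dose, takes children out before later values exist. These points limit the size of the problem and of the remedy.

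It would also be wrong to say that a falling child is imputed as an average child. The draw is conditional on arm and the child's own baseline, and includes residual variation.

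Finally, the protocol does not say that no other variable may enter, and a statistical analysis plan, not available here, could add some. But the predictors are named explicitly for the confirmatory analysis, so this is a stated choice rather than a detail left open.

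**Conclusion.** The point holds as a modest, cheaply corrected weakness in the confirmatory analysis. At the planned loss of about 10%, the treatment difference is unbiased if loss is random or relates to early haemoglobin alike in both arms; then only a little precision is given up. With selective loss in the MB arm only, the shift towards non-inferiority is about 0.03–0.11 g/dl, or 4% to 16% of the margin (0.03/0.7 and 0.11/0.7), and the one-sided error is about 3.4–6% instead of 2.5%. With selective loss in the PQ arm only, the bias has the opposite sign.

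These sizes rest on assumed correlations and assumed missingness mechanisms, none of which the protocol supplies. Shifts beyond this range need near-complete loss of the worst fallers from one arm, or more loss than planned. In the simulated scenarios, adding day-3 haemoglobin removed the bias; days 1 and 2 were not tested separately.

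**What to change.** In section 9, Confirmatory analysis, add haemoglobin on days 1, 2 and 3 to the fully conditional specification model as auxiliary variables, alongside treatment group and baseline haemoglobin. Keep the two-covariate model as a sensitivity analysis, so that the influence of the early values can be seen.

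Leave day 14 and day 28 values out, or use them only in a sensitivity analysis. A child lost for good after day 3 has none, and in other children they may follow the rescue treatment that section 6 allows between days 7 and 28.

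The cost is a slightly longer imputation model. The data are already scheduled, and the endpoint, margin and sample size do not change. The change cannot help children withdrawn at the first dose who have no later haemoglobin.
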